### Endpoints and variables

The primary endpoint will be the difference in mean days of hospital stay per year between patients included in the integrated and functional HC programs. Secondary endpoints will include the assessment of the differences between the two HC models i.e., mortality and hospital admissions, based on the IHI Triple Aim (Better Care, Better Health, Lower Costs) [26]. To this end, variables regarding subjects’ health status, quality of care, and resource utilization of patients included in the two models will be compared (Table 3). The demographic characteristics of the study participants will also be recorded.

**Table 3 Tab3:** Study variables

	Definition and Measurements	Categories
Demographic Characteristics		
Age	At the moment of entering the HC program	65–74 75–84 > 85
Gender		Male | Female
Health Status		
Caregiver	At the time of entering the HC program	Yes | No
Level of dependency	Scale defined by Royal Decree 174/2011; Law 39/2006 of Promotion of Personal Autonomy and Care for People in Situations of Dependency.	Grade I (25–49): Moderate dependency Grade II (50–74): Severe dependency Grade III (75–100): Great dependency
Decubitus ulcer	At physician’s discretion	Presence | absence
Drugs prescribed	By active substance.	Not polymedicated (< 5) Polymedicated (5–10) Hyperpolymedicated (> 10)
Comorbidity burden	Measured by Adjusted Morbidity Groups (GMA) risk assessment tool. GMA considers the type of disease (i.e. acute or chronic), number of systems affected, and complexity of each disease, which is coded by the International Classification of Diseases (ICD-9-CM) and stratify depending on the complexity.	31 qualitative ordinal GMA levels.
Mortality	Death during follow-up	Yes | No
Realization of CGA		Yes | No
Assessments included in CGA		
Performance of normal daily tasks	Barthel Scale [27]	Total dependency (< 20) Severe dependency (20–60) Moderate dependency (61–90) Mild dependency (91–99) Autonomous (100)
Mental health	Pfeiffer’s Test [28]	High risk (≤2) Mild cognitive impairment (3–4) Moderate cognitive impairment (5–7) Severe cognitive impairment
Decubitus ulceration risk	Braden Test [29]	High risk (< 12) Moderate risk (13–14) Low risk (15–18)
Social risk	TIRS [30]	There is social risk when one indicator over 6 is positive
Anxiety	Goldberg Scale [31]	Probable anxiety (≥4 positive responses) Probable depression (≥2 positive responses)
Geriatric depression scale	Yesavage Scale [32]	No depression (1) Possible depression (≥ 2)

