Mobility	Timed Up and Go Test [33]	Normal (< 10) Very little impaired (10–19) Moderately impaired (20–29) Severely impaired (≥30)
Comorbidity	Charlson Index [34]	No comorbidity (0–1) Low comorbidity burden (2) High comorbidity burden (> 3)
Social state	Social Scale [35]	No social risk (≤9) Social risk (10–14) Social problem (≥15)
Overburden of the caregiver	Zarit Test [25]	No overburden (< 46) Intense overburden (> 56)
Nutritional state evaluation	MNA [36]	Malnutrition (≤7) Malnutrition risk (8–11) Normal nutritional status (≥12)
Home adequacy	Revision of home adequacy to determine the need of social worker intervention	Social worker is recommended when at least one item is positive
Falls	Number of falls in the last year	–
Frailty	Gérontopôle Frailty Screening Tool [37]	Frailty identification if one item of the scale is positive.
Social services cost	Number and cost of social worker visits	–
Quality of life	EuroQOL 5D-3 L [24, 38, 39]	No problems (Level 1) Some problems (Level 2) Extreme problems (Level 3)
Quality of Care		
Physicians PQI	Prescription Quality Index of the physician [40]	Include assessment of three categories: More adequate therapeutic alternatives Hyper prescription of a particular group of drugs Selection indicators to promote safer and more effective alternatives available
Prescriptions	Number of prescription events per patient	–
Alternative drugs with therapeutic benefit	Percentage of use of the alternative drug as assessed by the physician	–
Shared Interdisciplinary Individual plan		Yes | No
Chronicity	Number of Complex Chronic Patients and Advanced Chronic Disease patients in the program	–
Satisfaction with health care received	IEXPAC Scale [23]	Satisfactory (=10) Unsatisfactory (< 10)
Overburden of the caregiver	Zarit Scale [25]	No overburden (< 46) Intense overburden (> 56)
Resource Utilization		
Family doctor visits	Number of at-home visits, other medical professional, primary care center or virtual appointments of the patient or the caregiver	–
Nursing staff visits	Number of at-home visits, other medical professional and primary care center appointments of the patient or the caregiver. Also, number of virtual consultations, including remote evaluation or by phone of medical record	–
Hospitalizations	Number of programmed, emergency and daycare admissions	–
Readmissions	Number of successive hospitalizations due to the same pathology in less than 30 days	–

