### Statistical analysis

The sample size calculation was based on an incidence of hospital admission of 40% and a reduction of 10% in the study group, a 2-year follow-up, and a 1:1 ratio for control and intervention groups. Under these constrains, a fixed alpha and beta errors of 5%, yielded an estimated size of 581 subjects per group. The statistical power of this sample, assuming alpha and beta errors of 5% was 85.3%.

All collected variables will be described for the overall study sample and for both study groups. Quantitative variables will be described as the mean and standard deviation (SD), and as the median and interquartile range (IR) for normally- and non-normally distributed variables, as confirmed by the Kolmogorov-Smirnov test. Categorical variables will be described as frequencies and percentages. Measures of central tendency will be compared using the T-test for independent samples or ANOVA, or their non-parametric counterparts: the Mann-Whitney U and Kruskal-Wallis tests. Categorical variables will be compared using the Chi-square test or Fisher’s exact test. If post hoc analyses are performed, the Bonferroni or the Games-Howell adjustments will be applied. Variables with differences in the bivariate analysis at baseline (*p* < 0.1) and those considered clinically relevant for the authors will be included in a linear multiple logistic regression to build a multivariate model to predict the difference in mean days of hospital stay and costs of patients in the HC program. To address Better Care and Better Health endpoints, the authors will apply a binary logistic regression for mortality and hospital admission variables; age, gender, and comorbidity burden will be included as adjustment variables. A backward stepwise regression will be used to avoid overfitting of the model obtained.

A significance threshold will be set at two-sided alpha value < 0.05. The analysis will be performed with SPSS (IBM Corp. Released 2012. IBM SPSS Statistics for Windows, Version 21.0. Armonk, NY: IBM Corp.).

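### Ordered categorical variables fall under a Chi-square/Fisher rule that ignores their order, costing roughly 8 to 10 points of power for a one-directional shift in a three-level variable

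*Protocol article*

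**What the plan says.** All references are to the protocol article.

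- **Statistical analysis**, categorical data: "Categorical variables will be compared using the Chi-square test or Fisher’s exact test". No separate rule is given for ordinal data.
- **Statistical analysis**, rank tests: these are named only as the alternative to the t-test and ANOVA when averages are compared, "or their non-parametric counterparts: the Mann-Whitney U and Kruskal-Wallis tests".
- **Statistical analysis**, regressions: the models cover hospital days, costs, mortality and hospital admission. None covers an outcome with ordered categories.
- **Endpoints and variables**: variables on health status, quality of care and "resource utilization of patients included in the two models will be compared (Table 3").
- **Table 3, Quality of life** (EuroQoL 5D-3L): "No problems (Level 1) Some problems (Level 2) Extreme problems (Level 3").
- **Table 3, Drugs prescribed** (by active substance): "Not polymedicated (< 5) Polymedicated (5–10) Hyperpolymedicated (> 10").
- **Table 3, Comorbidity burden**: "31 qualitative ordinal GMA levels". The authors therefore recognise that some of their variables are ordinal.

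**The concern.** A Chi-square or Fisher test on a three-level table asks whether the two distributions differ in any way at all. It gives the same answer if the labels of the levels are shuffled. The study's question has a direction: the Discussion expects the functional model to give better outcomes. For a consistent move towards better or worse levels, an unordered test spends 2 degrees of freedom where 1 would do, so a real shift is more likely to be missed. A significant result also need not mean that either model is better, since it can come from more patients at both extremes.

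EuroQoL is where this matters most. It is the study's health-related quality-of-life measure and one of the three questionnaires given at baseline and again at the final visit.

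**Working it through.** **1. The plan's own sample size.** The inputs are "an incidence of hospital admission of 40% and a reduction of 10% in the study group", beta 5%, a 1:1 ratio, and "A significance threshold will be set at two-sided alpha value < 0.05". I read the reduction as 10 percentage points, 40% against 30%; a relative reduction (40% against 36%) would need 3,824 per group.

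n = [1.960·√(2·0.35·0.65) + 1.645·√(0.40·0.60 + 0.30·0.70)]² / 0.10² = (1.322 + 1.103)² / 0.01 ≈ 589 per group. With unpooled variance it is 585. The stated 581 is reproduced to within 1.4% and is used below as the group size.

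The article also states 85.3% power for this sample. That figure does not reproduce (I get 94.8% at 581 per group) and belongs to hospital admission. It serves below only as a convenient reference level, next to 80%.

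**2. Cost of ignoring the order with three levels.** Power = P(noncentral χ² with df and noncentrality λ exceeds the 5% critical value). The critical value is 3.84 on 1 df and 5.99 on 2 df. For a proportional-odds shift over three levels, practically all of λ lies in the ordered component, so both tests have the same λ. With assumed control shares 40/45/15% and odds ratio 1.4, λ is 9.08 for each.

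| λ | Order-using test (1 df) | Chi-square (2 df) | Loss | Extra patients for Chi-square to match |
|---|---|---|---|---|
| 7.85 | 80.0% | 70.9% | 9.1 points | 23% |
| 9.06 | 85.3% | 77.3% | 8.0 points | 22% |

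**3. Check by simulation.** 581 per group, two-sided 5%, 40,000 runs per setting, Chi-square against tie-corrected Mann-Whitney. The article gives no category shares, so 40/45/15% in the control group is an assumption.

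| Common odds ratio | Chi-square | Mann-Whitney |
|---|---|---|
| 1.0 (type I error) | 4.9% | 4.9% |
| 1.2 | 29% | 37% |
| 1.3 | 55% | 65% |
| 1.4 | 77% | 85% |
| 1.5 | 91% | 95% |

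Three other assumed distributions (20/50/30, equal thirds, 60/35/5) give 48–58% against 58–68% at odds ratio 1.3. Over all four distributions the loss is about 7 to 11 points for odds ratios 1.2 to 1.4, and about 3 to 6 points at 1.5, where power is already high.

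**4. Number of drugs, with the two losses kept apart.** Assume an approximately normal count, cut at 4.5 and 10.5 to match the bands. Set the difference in means so that the uncut count has 85.3% power: difference = SD·√(2·9.06/581) = 0.177·SD, or 0.71 drugs for SD 4 and 0.62 for SD 3.5.

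For mean 8 and SD 4, the band shares are 19.1/54.3/26.6% against 24.2/54.6/21.1%. This gives λ = 7.21.

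| Assumed mean, SD | Count | Trend test on bands | Chi-square on bands | Loss from banding | Loss from ignoring order |
|---|---|---|---|---|---|
| 8, 4 | 85.3% | 76.6% | 66.9% | 8.7 | 9.7 |
| 9, 4 | 85.3% | 76.1% | 66.4% | 9.2 | 9.7 |
| 7, 3.5 | 85.3% | 75.3% | 65.5% | 10.0 | 9.8 |

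**5. The opposite case.** For a non-monotone difference, 30/40/30% against 25/50/25%, Chi-square has 88% power and Mann-Whitney 5%.

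**The case against.** The case on the other side has real force.

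- **Table 3 is not an analysis specification.** A reader might infer that the Categories column fixes how each variable is tested, because a dash appears where a variable stays numeric. Nothing in the article says so. The column also holds instrument content (the prescription index) and action guidance (home adequacy), and it shows reading bands for scores such as Barthel that could be analysed as scores. This stands: the link to Chi-square is an inference from the general rule and the table.
- **EuroQoL is not defined as one three-level outcome.** Levels 1 to 3 are response levels. A reader might infer that the plan wrongly omits an index score, but scoring may be left to the full protocol. This stands, so the point is limited to how the levels are compared.
- **Drugs prescribed is a weak example of an outcome.** It sits under Health Status with no stated follow-up time. Prescription events and pharmaceutical costs are recorded without bands. Nor does the article say that prescribing is a main target of the functional team; the extra nurse training it describes concerns chronic patients, fragility and palliative care. Its role here is as an illustration.
- **Chi-square is valid.** It holds its type I error, it detects non-monotone patterns that a rank test misses, and the reported percentages would show direction. All true, but a non-monotone pattern does not tell which model is better.
- **A statistical analysis plan may settle it.** Possibly. The article nevertheless states a rule without exception, and a plan that followed it literally would inherit the problem.

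**Conclusion.** The point holds as a modest weakness of a stated rule. As written, ordered variables that are to be compared between the models come under tests that ignore their order. For a one-directional shift in a three-level variable, the cost is about 8 to 10 points of power at the usual power levels. Testing the number of active substances in bands, if that is what is done, costs about 9 to 10 points more.

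A reader might add these two losses and charge the sum of 18 to 20 points to Chi-square. That would be wrong, because about half of it comes from banding, which is a separate choice.

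The figures rest on assumed category shares, proportional-odds shifts, an approximately normal drug count and 581 per group. The article gives none of the distributions. The direction of the loss holds for any consistent shift of this kind; its exact size does not. The primary endpoint (hospital days) and the named secondary endpoints (mortality, hospital admissions) are untouched. This is a worthwhile improvement and does not threaten the study's validity.

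**What to change.** Add to the Statistical analysis section:

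- Ordered categorical variables are compared with a test that uses the order: Mann-Whitney or a linear-by-linear trend test, or proportional-odds regression adjusted for age, gender and comorbidity burden. For EuroQoL this is applied to each dimension.
- The number of active substances is compared as a count, with the three bands kept for description.
- Chi-square and Fisher's exact test are kept for variables without an order.

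The cost is one or two sentences. No new data are needed, and Mann-Whitney is already in the plan. There are two small drawbacks: less sensitivity to non-monotone differences, which the reported percentages would still show, and a proportional-odds assumption to check if that model is chosen.

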Admissions to other public health care centers	Number of admissions, including convalescence, subacute, long-lasting and palliative units	–
Hospitalizations per year	Days hospitalized	–
Intermediate resources	Number and cost of laboratory tests, Radiology and interconsultations	–
Pharmaceutical costs	Expenditure per patient and medical professional during a year	–
Hospitalization-at-home device use	Number of activations per year and total of hospitalization days	–
Social services intensity	Monthly hours spent by the social worker. Costs derived from teleassistance, cleaning and cooking aid, reused orthopedic material and family worker	–
Call to emergency services	Number of patient intervention requests per year.	–
Perception of healthcare professionals	Qualitative, self-administered questionnaire of difficulties in HC practice, based on the survey reported by Linares et al. [20]	

*CGA* Comprehensive Geriatric Assessment, *HC* Home Care

Particularly, the baseline health status of study subjects will include the Gerontôpole frailty screening tool and the Adjusted Morbidity Groups (GMA) risk assessment tool, which considers the type of disease, number of systems affected, and complexity of each one [21, 37]. Additionally, a complete baseline Comprehensive Geriatric Assessment (CGA) will be performed, including the following assessments: the ability to perform normal daily tasks (Barthel scale), mental health status (Pfeiffer test), decubitus ulceration risk (Braden test), social risk (TRIS), geriatric depression (Yesavage scale), mobility status (Timed up & go test), comorbidity burden (Charlson Comorbidity Index), nutritional state (Mini-nutritional Assessment), and social status (Table 3) [27–35, 41]. The health-related quality of life of study participants and satisfaction of caregiver will be assessed at baseline and at the final follow-up visit using the EuroQoL IEXPAC and Zarit questionnaires, respectively [23–25].

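### The mortality and admission models name age, gender and comorbidity burden as adjusters and give no route for the frailty, function and cognition scores planned at baseline, so any centre difference in these would stay in the odds ratios

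*Protocol article*

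**What the plan says.** All references are to the protocol article.

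- **Statistical analysis, logistic models.** The authors plan a "binary logistic regression for mortality and hospital admission variables; age, gender, and comorbidity burden will be included as adjustment variables".
- **Statistical analysis, wider rule.** Covariates that differ at baseline (p < 0.1) or that the authors judge clinically relevant enter a different model, the one built "to predict the difference in mean days of hospital stay and costs of patients in the HC program".
- **Statistical analysis, selection.** "A backward stepwise regression will be used to avoid overfitting of the model obtained".
- **Endpoints and variables, text after Table 3.** "the baseline health status of study subjects will include the Gerontôpole frailty screening tool and the Adjusted Morbidity Groups (GMA) risk assessment tool", and "a complete baseline Comprehensive Geriatric Assessment (CGA) will be performed". The assessment lists Barthel for daily tasks and Pfeiffer for mental status.
- **Table 3.** GMA is built from type of disease, number of systems affected and disease complexity. Barthel, Pfeiffer and frailty have rows of their own. Whether the geriatric assessment was carried out is itself recorded as yes or no.
- **Study design and Discussion.** Each care model runs at one centre, and patients belong to a centre by where they live. The expectation of balance rests on age and GMA in the two reference populations.

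**The concern.** In a non-randomised comparison, the adjustment set decides how much of a group difference can be put down to the care model. Frailty, dependence in daily tasks and cognitive impairment plausibly predict death and admission in long-term home-care patients, and they can differ between two catchment areas at the same age, gender and GMA level. GMA as defined is a disease measure and does not stand in for them.

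The plan intends to measure all three at baseline, but nothing in the Statistical analysis section brings them into these two models. The resulting odds ratios are to carry the Better Care and Better Health conclusions, and the Discussion says the results may have important policy implications. A leftover difference in patient mix could be read there as an effect of the functional model, or could hide one.

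**Working it through.** **1. Can the three measures enter under the text as written?** There are three possible routes.

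- The named list holds age, gender and comorbidity burden.
- The p < 0.1 or clinical-relevance rule is attached to days of stay and costs.
- Backward selection starts from a given set and removes terms. It cannot add one, and the text does not exempt the three named adjusters or the group term from removal.

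None admits frailty, Barthel or Pfeiffer.

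**2. The plan's own sample size.** For admission of 40% v 30%, two-sided 5% alpha and 5% beta, the unpooled formula gives n = (1.960 + 1.645)² × (0.40×0.60 + 0.30×0.70) / 0.10² = 585 per group. The pooled version gives 589. The stated 581 is within 2% of both and is used below. (The stated 85.3% power does not follow: the power at 581 is 94.8%. That is a separate matter, and nothing here depends on it.)

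**3. How large could the confounding be?** The documents give no frailty, Barthel or Pfeiffer distribution by centre and no mortality rate for home-care patients. All inputs here except n are assumptions:

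- no true effect of the care model;
- two-year risk of 20% in less dependent patients;
- a share of severely dependent patients that is higher in the integrated group, taken as the difference left after age, gender and GMA;
- an odds ratio (OR) for death with severe dependency of 1.5 to 3.

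Formulas:

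- odds in severely dependent patients = OR × 0.20/0.80; risk h = odds/(1 + odds)
- group risk = p × h + (1 − p) × 0.20
- spurious group OR = odds(functional)/odds(integrated)
- z = risk difference / √{[r₁(1 − r₁) + r₂(1 − r₂)]/n}; rejection rate = Φ(z − 1.96) + Φ(−z − 1.96)

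Worked case, 50% v 40% and OR 3: odds 0.75, h = 0.4286. Integrated: 0.5 × 0.4286 + 0.5 × 0.20 = 31.4%. Functional: 0.4 × 0.4286 + 0.6 × 0.20 = 29.1%. Group OR 0.90. The standard error is 0.02695, z = 0.02286/0.02695 = 0.85, and the rejection rate is 13.6%.

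| Severely dependent, integrated v functional | OR for death | Risk, integrated v functional | Spurious group OR | Rejection rate (nominal 5%) |
|---|---|---|---|---|
| 45% v 40% | 1.5 | 23.3% v 22.9% | 0.98 | 5.2% |
| 45% v 40% | 2 | 26.0% v 25.3% | 0.97 | 5.8% |
| 45% v 40% | 3 | 30.3% v 29.1% | 0.95 | 7.1% |
| 50% v 40% | 2 | 26.7% v 25.3% | 0.93 | 8.1% |
| 50% v 40% | 3 | 31.4% v 29.1% | 0.90 | 13.6% |
| 50% v 30% | 3 | 31.4% v 26.9% | 0.80 | 40% |

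The direction is assumed too. If the functional centre had the more dependent patients, the bias would run against it.

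For admission, with the integrated group set at the plan's 40%, the same kind of calculation gives 5.3% (50% v 45%, OR 1.5), 14.6% (50% v 40%, OR 3) and 43.9% (50% v 30%, OR 3).

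**4. Is there room for the extra terms?** At the planned size, about 581 × 0.40 + 581 × 0.30 = 407 patients are admitted. Even with categorised covariates, 13 parameters (group 1, age 2, gender 1, GMA 1, frailty 1, Barthel 4, Pfeiffer 3) leave 407/13 = 31 events each. If only the regional 5% of the 3480 + 2970 residents aged 65 or over were in home care (an assumption, about 322 patients or 161 per group), there would be about 161 × 0.70 = 113 admissions. With age and scores as linear terms (7 parameters) that is about 16 each.

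**The case against.** **The list is not declared closed.** The article does not say that only these three variables will be used, and a backward step against overfitting makes little sense for three covariates, which may hint at a longer list. That sentence may equally refer to the other model. The text names a set for these endpoints and ties the wider rule elsewhere, so the point stands as a statement about what is written.

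**The scores are post-exposure.** Both care models were already running, and eligibility requires at least 3 months in the programme. Barthel or frailty may already reflect the care model, and adjusting could remove part of a real early effect. This stands as a limit. GMA, already in the model, raises the same question.

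**The scores may be measured differently by arm.** The Discussion warns that one team makes all assessments in the functional group and several observers do so in the integrated group. This also stands, and is a reason to show both models.

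**Stronger readings that the documents do not support.**

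- A reader might infer from Table 2 that frailty differs between the centres. Table 2 describes whole reference populations, not home-care patients. Its age differences concern a variable already in the models, and its mortality difference has P = 0.143. It should not be cited as evidence of a frailty difference.
- A reader might infer that the scores will exist for every patient. They are planned for the study subjects, but recording completion of the assessment as yes or no allows for gaps.
- A reader might infer that the primary result is affected. The days-of-stay model can take in these variables under its own rule.

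**Conclusion.** The concern holds as a conditional one. The text fixes a short adjustment set for mortality and admission and leaves out three plausible confounders that it plans to measure, in a design where adjustment is the main protection against differences in patient mix. Confounding enters these odds ratios only to the extent that frailty, function or cognition differ between the centres beyond age, gender and GMA, and no document shows that they do.

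Under the assumed inputs the effect runs from negligible (false-positive rate about 5%) through moderate (14%) to serious (40%). The upper figures need a 10- to 20-point residual imbalance, an odds ratio of 3 and the full 581 per group. At the assumed 161 per group, the 50% v 40% case gives 7.3%, although its spurious OR of 0.90 is unchanged. Because the imbalance cannot be known in advance and overfitting is no obstacle at the planned size, these covariates are better fixed beforehand than left out. Adding them cannot remove all centre-level confounding, since each care model has one centre.

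**What to change.** In the Statistical analysis section, state that:

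- the mortality and hospital-admission logistic models each include group, age, gender, GMA, baseline frailty (Gérontopôle tool), Barthel and Pfeiffer, with scores as continuous terms;
- group and these confounders are kept out of backward deletion;
- patients without a completed geriatric assessment are handled by a stated missing-data method such as multiple imputation, so that they are not dropped;
- the three-variable model is reported beside the wider one, so that readers can see how far the added scores move the odds ratio.

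Report the limits with the results: scores taken after at least 3 months in the programme, different observer structures by arm, and centre confounding that patient covariates cannot remove.

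The cost is a change of wording and a few more model terms. No new data collection is needed, because the measures are already planned, but the missing-data step adds some analysis work.
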